## Methods and analysis

### Study design

PROPULSION SANTÉ (NCT06981169) is a prospective multicentre observational study conducted in patients aged ≥6 years referred by primary care for a diagnostic respiratory function test (BDR or metacholine BPT) for suspected asthma. Participants will undergo FeNO and BEC measurements during their visit for stratification. If BDR is non-diagnostic, patients will undergo a methacholine BPT and may also be invited to participate in one of the two translational sub-studies—DIVE for adults (NCT05992519) and DIVE2 for children (NCT07011394)—the latter sub-studies involve additional procedures, including blood sample collection and non-invasive nasal sampling using nasosorption (figure 1). Participants will also have the option to preserve their data and/or samples in the Quebec Respiratory Health Research Network Biobank (www.biobanque.ca).

**Figure 1 F1:**
[figure not shown]
Overlap between the Propulsion Santé and DIVE studies. All patients referred by primary care for suspected asthma will be invited to participate in PROPULSION SANTÉ, forming the *base* of the iceberg, representing the broader population. The *tip* represents the DIVE (≥18 years) and DIVE-2 (6–17 years) studies, which include a smaller group of patients invited based on more selective inclusion and exclusion criteria. These two translational research studies focus on investigating type 2 inflammatory pathways through the analysis of serum, NELF and urine samples. These two translational research studies focused on investigating type 2 inflammatory pathways through the analysis of serum, NELF and urine samples. BEC, blood eosinophil count; FeNO, fraction of exhaled nitric oxide; NELF, nasal epithelial lining fluid.

### Setting

The study will be conducted at three Quebec medical centres: CHUS, CHUSJ and MHC-MUHC. A dedicated research respiratory therapist will be assigned to each centre for 1 year to facilitate recruitment through convenience sampling. With participant consent, longitudinal follow-up by email will occur at 4, 8 and 12 months after the initial diagnostic visits.

### Participants

Eligible participants are individuals aged ≥6 years who present with symptoms suggestive of asthma and have been referred by primary care (family physicians and nurse practitioners) or community practice (eg, paediatricians and other non-pulmonologist physicians) for asthma diagnosis at one of the three participating centres. Participants are identified from an existing waiting list of approximately 3000 patients awaiting respiratory function testing. The only exclusion criterion for PROPULSION SANTÉ is refusal to participate in the study.

Among these patients, a target sample of 123 adult participants (aged≥18 years) and 123 paediatric participants (aged 6–18 years) undergoing BPT will be consecutively invited to participate in the DIVE and DIVE-2 sub-studies, respectively, regardless of their T2 status. DIVE/DIVE2 inclusion requires non-diagnostic spirometry and no contraindication to methacholine challenge. Patients will be excluded from participation if they meet any of the following conditions: use of inhaled or systemic corticosteroids within 48 hours prior to testing; tobacco use within the previous 6 hours; diagnosis of chronic obstructive pulmonary disease (COPD), defined as all of the following — age ≥40 years, fixed airway obstruction on spirometry (FEV1/Forced Vital Capacity (FVC)<0.7) and a smoking history >10 pack-years or documented alpha-1 antitrypsin deficiency— and evidence of parenchymal lung disease (such as cystic fibrosis or bronchiectasis), unstable cardiac disease or a history of acute respiratory infection (viral or bacterial) within the preceding 4 weeks.

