Objective testing is essential for accurate asthma diagnosis, especially given high rates of overdiagnosis estimated at 33% in adults and 44% in children in Canada.^20^ Relying on subjective clinical criteria for asthma diagnosis has led to disease overestimation, impacting treatment decisions and healthcare resources.^21^ Spirometry is recommended to demonstrate post-bronchodilator reversibility (BDR), an increase in forced expiratory volume in 1 s (FEV1) ≥200 mL and ≥12% in adults and ≥12% in children and adolescents).^6^ However, spirometry is inconclusive in up to 80% of cases (and over 60% in children), necessitating a methacholine bronchial provocation test (BPT).^22 23^ Furthermore, identifying post-bronchodilator reversibility is of doubtful clinical consequence, as associated with other diseases (eg, chronic obstructive pulmonary disease) and unrelated to the risk of asthma attacks.^24 25^

Methacholine BPT is a relatively cumbersome procedure, requiring monitoring by specialised hospital units and significant testing time, which limits accessibility. These constraints contribute to both over-diagnosis and under-diagnosis, with significant individual, societal, environmental and economic consequences.^1421 26^,^28^

Inadequate access to objective tools in primary care delays or impairs treatment, worsening asthma control, quality of life and healthcare costs.^6 21^ Zafari *et al* estimated that improved diagnostic algorithms reducing sub-optimal asthma control by 10% could save $50.5 billion over 20 years in Canada.^4^

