In patients consenting to participate in the DIVE or DIVE2 sub-study, supplementary biological samples will be collected during the methacholine visit, including the additional blood samples, nasosorption test for NELF and urine. The total volume of blood drawn from a child will adhere to Quebec’s standards for maximum blood volumes based on weight.^36^

Participants will then undergo spirometry or BPT with methacholine, depending on the visit, as per the diagnostic procedure.

Spirometry will be performed according to American Thoracic Society (ATS)/European Respiratory Society (ERS) standards, with reference values derived from the Global Lung Initiative 2022 race-neutral prediction equations.^47^ Patients will have been informed in advance of the need to withhold treatment as outlined in table 1.^48 49^

**Table 1 T1:** Recommended inhaler washout period prior to testing^48 49^

	Washout period	
	Spirometry	Bronchial provocation test
Short-acting β₂-agonists	> 4 hours	> 6 hours
Short-acting muscarinic antagonists	> 12 hours	> 12 hours
Long-acting β₂-agonists	> 36 hours	> 48 hours
Long-acting muscarinic antagonists	> 48 hours	> 1 week

Diagnostic criteria for asthma include:

Bronchodilator Reversibility Test: An increase in FEV₁ of ≥12% from baseline for all participants, with an additional criterion of ≥200 mL absolute improvement required for adults (≥18 years). Bronchodilator administration will be standardised using salbutamol 400 mcg delivered via spacer device.Methacholine BPT: Airway hyper-responsiveness, defined as a provocative dose causing a 20% decrease in FEV₁ (PD₂₀) of <400 mcg (equivalent to a provocative concentration (PC₂₀) of<16 mg/mL). While we acknowledge the more stringent European threshold (PD₂₀ ≤200 mcg, equivalent to PC₂₀ ≤8 mg/mL), we will adhere to our institutional protocols.^1^,^3^ The latter (European) diagnostic threshold will be evaluated through pre-planned sensitivity analyses.

At the end of the visit, all participants will complete a satisfaction questionnaire regarding the inflammatory biomarker testing and overall visit experience.

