#### Secondary Outcomes

Diagnostic accuracy of inflammometry assessed through receiver operating characteristic (ROC) curve analyses using FeNO levels, BEC and their combined values, with BPT as gold standard. Clinically relevant thresholds will be identified to optimise rule-in capacity for asthma diagnosis in primary care, targeting ≥90% of specificity and a positive likelihood ratio (LR+) ≥10 in children, adolescents and adults (as three distinct subgroups).Assessment of inflammatory status on asthma control, evaluated pre-diagnosis and post-diagnosis using the ACQ-5, ACT and EQ-5D-5L questionnaire scores. Additional measures include the number of exacerbations, prescribed and dispensed medications and the frequency of specialised asthma consultations collected from clinical records, drug claims and patient electronic reports at baseline and at 4-month, 8-month and 12-month follow-up.Assessment of health benefits in terms of QALY, budget impact and economic efficiency (evaluated using incremental cost-effectiveness ratio (ICER) and Incremental cost-utility ratio (ICUR)) of integrating inflammatory biomarkers into primary care asthma diagnosis.The evaluation of annualised carbon dioxide (CO2) emissions from inhalers dispensed to non-asthmatic individuals awaiting their diagnostic tests was done based on drug claims and Cascades Canada environmental data.^27^ Environmental sustainability assessment of biomarker-enabled pathways will be explored.Descriptive analysis of patient satisfaction regarding inflammometry and the overall experience of diagnostic procedures, with responses stratified by age (6–<12, 12–<18, ≥18) and diagnostic test (BDR or BPT) and final asthma diagnosis status.

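### The inhaler CO2 outcome includes inhalers dispensed for COPD or parenchymal lung disease, so it can overstate the emissions that faster asthma testing could avoid

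*Protocol article*

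**What the plan says.** All places are in the protocol article.

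- **Participants, main study.** Eligible people have "symptoms suggestive of asthma and have been referred by primary care" or community practice. On exclusions: "The only exclusion criterion for PROPULSION SANTÉ is refusal to participate in the study".
- **Participants, DIVE and DIVE-2.** The sub-studies exclude a "diagnosis of chronic obstructive pulmonary disease (COPD), defined as all of the following": age 40 or over, fixed obstruction (FEV1/FVC below 0.7), and either more than 10 pack-years or alpha-1 antitrypsin deficiency. They also exclude "evidence of parenchymal lung disease (such as cystic fibrosis or bronchiectasis").
- **Study visits, diagnostic criteria.** Asthma is "An increase in FEV₁ of ≥12% from baseline for all participants" (plus 200 mL in adults) or "Airway hyper-responsiveness, defined as a provocative dose causing a 20% decrease in FEV₁ (PD₂₀) of <400 mcg". Neither criterion carries a condition on another lung disease.
- **Secondary Outcomes.** The environmental outcome is annualised CO2 "emissions from inhalers dispensed to non-asthmatic individuals awaiting their diagnostic tests", taken from drug claims. Statistical methods says it will be analysed descriptively.
- **Discussion and Conclusion.** Lower inhaler emissions are listed among the anticipated benefits. The Conclusion describes the inhalers used during diagnostic delay as unnecessary, and says their impact may potentially be reduced.

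**The concern.** The CO2 outcome is meant to show how much inhaler use could be avoided if people without asthma were identified sooner. That reading needs a group whose inhalers are there because asthma is suspected. The plan instead defines the group by a negative asthma test, and a negative asthma test does not mean the absence of lung disease.

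A participant with COPD or bronchiectasis whose tests are negative is correctly non-asthmatic. Inhalers dispensed for that disease would still be expected after a prompt test, yet they are added to the total. The error runs one way, towards a larger apparent environmental gain. The authors already have an operational COPD definition and apply it to the sub-studies, so the omission is easy to repair.

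**Working it through.** The article gives no figure for this outcome to reproduce. The check is a comparison of the rules, followed by arithmetic on assumed inputs.

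**Step 1: follow one participant through the rules.** Take an adult with COPD under the sub-study definition, referred for suspected asthma.

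1. Eligible for the main study, since refusal is the only exclusion.
2. BDR and BPT negative: labelled non-asthmatic.
3. Inhalers dispensed while waiting are counted in the CO2 outcome. The article describes no separation by indication.

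**Step 2: look for an analysis that removes this participant.** Statistical methods lists a sensitivity analysis without active smokers. It keeps ex-smokers with COPD and people with alpha-1 deficiency or bronchiectasis. The smoking-status strata apply to the primary analyses. The other sensitivity analyses drop the paediatric-only sites or change the BDR and BPT thresholds. Pulmonologists interpret the tests (Intervention), but no rule for another diagnosis is stated. None of these removes the participant from the CO2 outcome.

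**Step 3: possible size.** Let s be the share of non-asthmatic adults with COPD or parenchymal disease, and r their inhaler emissions per person relative to the rest. Both are assumptions. Their share of adult emissions is s·r / (s·r + 1 − s).

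| s | r = 1 | r = 3 | r = 6 |
|---|---|---|---|
| 5% | 5% | 0.15/1.10 = 14% | 0.30/1.25 = 24% |
| 10% | 10% | 0.30/1.20 = 25% | 0.60/1.50 = 40% |
| 20% | 20% | 0.60/1.40 = 43% | 1.20/2.00 = 60% |

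The outcome covers all ages. Assume that adults are half of the non-asthmatic group, that no child is affected, and that unaffected adults and children emit equally. Then s halves:

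- s = 5%, r = 3: 0.075/(0.075 + 0.975) = 7%.
- s = 20%, r = 6: 0.60/(0.60 + 0.90) = 40%.
- r = 1: 2.5% to 10%.

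**Step 4: does the same gap move the adult biomarker cut-offs?** Illustration, all inputs assumed: among BPT-tested adults without COPD, 40% have asthma. Median FeNO is 35 ppb with asthma and 20 ppb without, with log-SD 0.65.

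- Without COPD, the 90%-specificity cut-off is 20 × exp(1.2816 × 0.65) = 46 ppb. Sensitivity is 0.337, so LR+ = 0.337/0.10 = 3.4.
- Now let 20% of those tested have COPD with median FeNO 20 ppb, 60% of them BPT-positive. The positive label holds 0.80 × 0.40 = 0.32 asthma and 0.20 × 0.60 = 0.12 COPD. The cut-off stays at 46 ppb. Apparent sensitivity is (0.32 × 0.337 + 0.12 × 0.10)/0.44 = 0.27, so LR+ = 2.7.
- In simulations with COPD at 5-20% of those tested, COPD median FeNO 15 or 20 ppb, and 30-60% of COPD BPT-positive, the cut-off lay between 44 and 46 ppb and the apparent LR+ between 2.7 and 3.3.

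So the cut-off barely moves. What can be biased is sensitivity and LR+.

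**The case against.** **The broad population is deliberate, and the affected group may be small.** The Figure 1 caption presents the main study as the wider population and the sub-studies as more selective. Eligibility requires suspected asthma. The COPD definition starts at age 40, two of the three sites are paediatric-only, and Sample size puts about half the waiting list in children. All of this stands. It rules out calling the different criteria a contradiction, and it could make the effect small. It does not take affected adults out of the CO2 total.

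**It may belong to an analysis plan or full protocol that is not shown.** A separation by indication may exist there, and if so the point is settled. As the article states the outcome, however, the population is simply everyone non-asthmatic, and following it produces the error.

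**The outcome is secondary and descriptive, and the Conclusion is hedged.** This stands and sets the severity.

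**Stronger reading: that the adult cut-offs are distorted.** A reader might infer this from the Introduction, which describes reversibility "as associated with other diseases (eg, chronic obstructive pulmonary disease) and unrelated to the risk of asthma attacks". The article does not support it. That sentence concerns BDR, while the ROC analysis takes BPT as its reference standard and BPT follows a non-diagnostic BDR. A COPD patient labelled asthmatic by BDR does not enter the ROC through that label. BPT-negative COPD patients are correctly non-asthma and belong in a real-world accuracy sample. Only BPT-positive COPD is mislabelled, and Step 4 shows little movement in the cut-off.

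**Conclusion.** The point holds for the CO2 outcome. As written, it counts inhalers dispensed for COPD or parenchymal lung disease together with those that the Conclusion calls unnecessary, and no listed analysis separates them. The bias can only raise the apparently avoidable emissions.

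Its size cannot be fixed from the article. The ranges in Step 3 rest wholly on assumed shares and emission ratios. They run from the patients' own share of the group, where emissions per person are equal, to more than half of adult emissions at the top of the assumed range.

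A reader might also infer that these patients should not be enrolled. That does not follow: they are part of the referred population and belong in the delay analysis. For diagnostic accuracy, only a possible bias in adult sensitivity and LR+ remains.

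Severity: minor.

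**What to change.** 1. Leave enrolment and the diagnostic-delay analysis as they are.
2. Derive one flag for participants who meet the COPD criteria in Participants or have recorded parenchymal lung disease. Use spirometry from any study visit, because Figure 2 shows that some patients go straight to BPT, together with smoking and medical history. That section gives only examples of parenchymal disease, so state which recorded diagnoses count.
3. Report the CO2 outcome for non-asthmatic participants without the flag, with the all-comers total beside it. Base any statement about avoidable emissions on the first figure.
4. Optionally, repeat the adult ROC analysis without flagged participants, beside the all-comers analysis, and compare sensitivity and LR+.

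Cost: a few sentences of analysis wording, one derived variable and a slightly smaller adult set for these analyses. Study visits names smoking status only, and the full variable list (online supplemental table S2) is not shown. Confirm early that pack-years and alpha-1 antitrypsin deficiency are recorded, since the flag needs them.

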### Study visits

Study visits will coincide with medically recommended testing for suspected asthma (pre-/post-bronchodilator spirometry followed, if negative, with methacholine). Biobanking for DIVE and DIVE2 will only be conducted during methacholine visits. Electronic informed consent (and assent when applicable) will be obtained via REDCap.^33 34^ Additional data will be gathered on asthma exacerbation history and healthcare resource utilisation over the preceding year, including medications, by the use of reMed,^35^ a provincial research data repository of community pharmacy dispensed drugs that covers individuals under the public drug insurance plan.

During the single study visit, baseline bio-anthropometric and clinical data (age, sex, ethnicity, height and weight) will be collected. Participants will be interviewed regarding their medical history (smoking status, respiratory medication (with simultaneous carbon footprint calculation based on the number and type of inhalers delivered), recent (< 6 last weeks) respiratory infection and allergic history. Patients (and their legal guardian, if applicable) will complete standardised questionnaires on asthma control for the last 4 weeks (Asthma Control Questionnaire 5 (ACQ-5),^36^ Asthma Control Test (ACT)^37^ in adults and childhood Asthma Control Test (c-ACT) for children^38^ and of quality-adjusted life years (QALY) (EuroQol Five Dimensions Five Levels (EQ-5D-5L)^39 40^ for adults and EuroQol Five Dimensions Youth (EQ-5D-Y)^41^ for children).

Research respiratory therapists will first measure FeNO during a 10 s exhalation (6 s for children unable to cooperate, with a 10- s expiration)^31 42^ using NIOX VERO device (approved by Health Canada as a clinical tool). The latter was selected based on its established precision (coefficient of variation <10%), reproducibility and clinical validation.^43 44^ Then, blood samples will be collected for BEC either via capillary puncture (preferred for children), using the single-use Tasso+blood collection device (approved by Health Canada), or by venipuncture.^45^ For children, an anaesthetic cream, Ametop GEL 4% (tetracaine hydrochloride gel), will be offered to be applied to the puncture site 30 min before blood collection.^46^

In patients consenting to participate in the DIVE or DIVE2 sub-study, supplementary biological samples will be collected during the methacholine visit, including the additional blood samples, nasosorption test for NELF and urine. The total volume of blood drawn from a child will adhere to Quebec’s standards for maximum blood volumes based on weight.^36^

Participants will then undergo spirometry or BPT with methacholine, depending on the visit, as per the diagnostic procedure.

Spirometry will be performed according to American Thoracic Society (ATS)/European Respiratory Society (ERS) standards, with reference values derived from the Global Lung Initiative 2022 race-neutral prediction equations.^47^ Patients will have been informed in advance of the need to withhold treatment as outlined in table 1.^48 49^

**Table 1 T1:** Recommended inhaler washout period prior to testing^48 49^

	Washout period	
	Spirometry	Bronchial provocation test
Short-acting β₂-agonists	> 4 hours	> 6 hours
Short-acting muscarinic antagonists	> 12 hours	> 12 hours
Long-acting β₂-agonists	> 36 hours	> 48 hours
Long-acting muscarinic antagonists	> 48 hours	> 1 week

Diagnostic criteria for asthma include:

Bronchodilator Reversibility Test: An increase in FEV₁ of ≥12% from baseline for all participants, with an additional criterion of ≥200 mL absolute improvement required for adults (≥18 years). Bronchodilator administration will be standardised using salbutamol 400 mcg delivered via spacer device.Methacholine BPT: Airway hyper-responsiveness, defined as a provocative dose causing a 20% decrease in FEV₁ (PD₂₀) of <400 mcg (equivalent to a provocative concentration (PC₂₀) of<16 mg/mL). While we acknowledge the more stringent European threshold (PD₂₀ ≤200 mcg, equivalent to PC₂₀ ≤8 mg/mL), we will adhere to our institutional protocols.^1^,^3^ The latter (European) diagnostic threshold will be evaluated through pre-planned sensitivity analyses.

At the end of the visit, all participants will complete a satisfaction questionnaire regarding the inflammatory biomarker testing and overall visit experience.

Participants will be followed longitudinally via email correspondence at 4, 8 and 12 months following diagnostic confirmation. At each time point, participants will complete questionnaires covering the period since the last follow-up. Data will be collected on prescribed and dispensed medications, medication use, symptom evolution, exacerbations, health-related quality of life (measured by the EQ-5D-5L), frequency of exacerbations, healthcare utilisation and asthma control (assessed using the ACQ-5 and ACT).

All collected variables are indicated in online supplemental table S2.

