### Intervention

The interpretation of respiratory function tests and biomarkers will be performed by the principal investigator pulmonologist at each centre or by trained designated collaborating pulmonologists by following these models:

High-risk inflammatory asthma is defined by FeNO ≥25 ppb or BEC ≥300 cells/µL in participants ≥12 years (≥20 ppb or ≥300 cells/µL in children aged 6 to <12 years)^15 50^ : one or more elevated biomarkers will be interpreted as a high risk of asthma exacerbation. If spirometry is non-diagnostic, BPT will be prioritised (<2–4 weeks).Low risk inflammatory asthma is defined by FeNO <25 ppb and BEC <300 cells/µL (<20 ppb or <300 cells/µL in children aged 6–<12 years)^15 50^: this will be interpreted as a low risk of asthma exacerbation. If spirometry is non-diagnostic, BPT will be scheduled according to the standard waiting list.

Results of biomarkers will be integrated on the medical report indicating the probability (high/low) of asthma exacerbation and suggested management with either ICS taken as-needed (T2-low) or regularly (T2-High) ICS if clinically appropriate, which will be forwarded to the referring physician.

The patient test pathway based on their respiratory test and the results of the inflammometry assessment is summarised in figure 2.

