For the primary outcome of waiting time differences, the baseline diagnostic delay, prior to the project implementation, will be established based on the time elapsed between the initial request for an asthma diagnostic test made by primary care and the performance of that test. During the intervention, diagnostic delays will be monitored prospectively, both overall and stratified by inflammatory status. We will apply linear mixed-effects models with restricted maximum likelihood estimation. These models will incorporate (high-risk vs low-risk), study period at time of inclusion, and the number of awaiting tests as fixed effects. Random effects will account for within-centre clustering and repeated measurements. In addition, Kaplan-Meier survival curves will be constructed to visualise the probability of remaining undiagnosed over time for both high-risk and low-risk inflammatory phenotypes. These curves will allow for a graphical representation of differences in diagnostic efficiency between groups. Cox proportional hazards regression will be used to identify significant predictors of waiting time with HRs and 95% CIs reported.

Diagnostic performance in the secondary outcome will be evaluated through ROC analysis, calculating the area under the curve (AUC) with 95% CIs for each individual marker and for their combined use. Sensitivity, specificity, positive and negative predictive values and likelihood ratios will be calculated with their respective 95% CIs.

Health utility values will be derived from EQ-5D questionnaires^39 52 53^ completed at baseline and follow-up visits. Quality-adjusted life years will be calculated using the AUC method, connecting utility values across measurement time points. This approach integrates health-related quality of life over the 12-month follow-up period. To assess the financial implications of implementing FeNO testing within the provincial healthcare framework, we will develop a budget impact model for the MSSS. Environmental and satisfaction-related outcomes will be analysed using descriptive statistics. CO₂ emissions from inhalers dispensed to non-asthmatic individuals will be estimated based on Cascades Canada data,^27^ and patient satisfaction with inflammometry will be assessed using structured questionnaires.

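### Follow-up is given two different start dates that diverge by biomarker group, and the follow-up text drops the children's baseline questionnaires (c-ACT, EQ-5D-Y)

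*Protocol article*

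**What the plan says.** **Start of follow-up.** Under Setting, "longitudinal follow-up by email will occur at 4, 8 and 12 months after the initial diagnostic visits". Under Study visits, "Participants will be followed longitudinally via email correspondence at 4, 8 and 12 months following diagnostic confirmation". The Abstract and Secondary Outcomes give only baseline plus 4, 8 and 12 months. Study visits adds that each questionnaire covers the time since the previous follow-up.

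**Baseline.** "During the single study visit, baseline bio-anthropometric and clinical data (age, sex, ethnicity, height and weight) will be collected". The article does not say which visit is baseline when a patient attends once for reversibility testing and again for BPT.

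**Time between the tests (Intervention).** For patients with at least one raised biomarker: "If spirometry is non-diagnostic, BPT will be prioritised (<2–4 weeks"). For the others: "If spirometry is non-diagnostic, BPT will be scheduled according to the standard waiting list".

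**QALYs (Statistical methods).** Utilities from baseline and follow-up EQ-5D are joined by the area-under-the-curve method. "This approach integrates health-related quality of life over the 12-month follow-up period". No start date is given for that period.

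**Instruments.** At baseline, Study visits assigns ACT and EQ-5D-5L to adults, and c-ACT and "EuroQol Five Dimensions Youth (EQ-5D-Y") to children; ACQ-5 is also listed. At follow-up the measures are "health-related quality of life (measured by the EQ-5D-5L), frequency of exacerbations, healthcare utilisation and asthma control (assessed using the ACQ-5 and ACT"). Secondary Outcomes names the same three instruments (ACQ-5, ACT, EQ-5D-5L) for the comparison before and after diagnosis. No paediatric version appears in either place.

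**The concern.** The two start dates coincide for a patient diagnosed at reversibility testing or referred directly to BPT. They separate for anyone who needs BPT after a non-diagnostic first test, and the Introduction puts inconclusive spirometry at up to 80% of cases (over 60% in children). The size of the gap is set by biomarker status, which is the grouping variable. The ambiguity is therefore not noise shared equally by both groups. Depending on how the follow-up emails are triggered, QALYs, exacerbation counts and healthcare use would be collected at different stages of the pathway, or over different lengths of time, in the two groups. The wait is also where any benefit of earlier diagnosis would show.

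Diagnostic confirmation is moreover an event that some participants may never have (asthma ruled out) or have not yet had (BPT pending). If it triggers the emails, follow-up could become conditional on the test result or on having been tested.

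The instrument problem is independent of this. A utility curve that begins on EQ-5D-Y and continues on EQ-5D-5L is not on one scale, and a c-ACT score at baseline set against an ACT score later is not a change on one measure.

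**Working it through.** The article states no figure that depends on this point, so there is nothing to reproduce. The check compares the two wordings and then does simple window arithmetic.

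**Inputs**
- W = months from the reversibility visit (taken as baseline) to BPT.
- Biomarker-high: BPT within 2–4 weeks (Intervention), so W is about 0.5 to 1.
- Biomarker-low: standard list (Intervention). The Introduction reports waits of more than 1 year for pending tests but gives no separate figure for the interval between the two tests. W = 6 and W = 12 are therefore assumptions.
- QALY window: 12 months (Statistical methods).

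**Formulas**
- Start at the first visit: the window runs from 0 to 12, and the waiting months inside it are min(W, 12).
- Start at confirmation: the window runs from W to W + 12, and the waiting months inside it are 0.
- Start at confirmation, but with the curve drawn from the baseline utility: span W + 12, first interval W + 4, and no utility measured during the wait.

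**Results**

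| W (months) | Waiting months in window, visit start | Waiting months in window, confirmation start | Span from baseline, confirmation start | First interval from baseline, confirmation start |
|---|---|---|---|---|
| 1 | 1 of 12 (8%) | 0 | 13 | 5 |
| 6 | 6 of 12 (50%) | 0 | 18 | 10 |
| 12 | 12 of 12 (100%) | 0 | 24 | 16 |

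With a visit start, the first recall interval is 4 months for everyone. With a confirmation start, it is either 4 months (leaving the wait uncovered) or W + 4 months (unequal by group).

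**Effect on the comparison before and after diagnosis.** With a visit start, the questionnaires fall at 4, 8 and 12 months. If W = 1, all three follow BPT. If W = 6, two do. If W = 12, the first two precede BPT and the third coincides with it. Neither start date is free of cost.

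**Instruments for children, side by side**

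| Measure | Baseline | Follow-up and before/after comparison |
|---|---|---|
| Utility | EQ-5D-Y | EQ-5D-5L |
| Control test | c-ACT | ACT |
| ACQ-5 | Listed; unclear whether the adult qualifier applies to it | Listed |

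The first two rows do not match. The third may.

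**The case against.** Several points on the other side are fair.

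- *The Setting wording is plural.* Initial diagnostic visits could loosely cover both the reversibility and the BPT visit, which brings it nearer to the other wording. This narrows the contradiction but still fixes no date.
- *Negative patients do have a usable date.* The primary outcome is timed to the final diagnostic test performed, and a patient with asthma ruled out has that date too. This is a sensible reading, but the follow-up text does not adopt it, and it gives no date to a patient whose BPT is pending.
- *The instrument list may be shorthand.* Statistical methods refers only to EQ-5D questionnaires, and Study visits points to supplemental table S2, which was not available and may name the youth versions. Even so, the article separates instruments by age at baseline and then, in two later places, names a set without the paediatric ones. That text needs correcting whatever the table says.

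A reader might also infer more than the documents support:

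- *That no paediatric change score can be computed.* ACQ-5 appears at both times and may apply to children, and changes among the 4, 8 and 12 month points remain available.
- *That the wait is wholly unobserved under the confirmation wording.* The curve may start at the baseline utility, the first recall may reach back to baseline, and exacerbations, medications and consultations also come from clinical records and drug claims. The problem is then unequal spans.
- *That a known QALY loss per patient goes uncounted.* This would need both the wait between the two tests and the utility cost of waiting, and the article gives neither.
- *That close to half of participants are affected by the instrument change.* The paediatric figures (1300 or about 1500 of about 3000) describe pending tests, not the convenience sample to be recruited.

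**Conclusion.** The point stands as an inconsistency in the stated text, in two parts. First, two start dates are given for the same questionnaires. They diverge for patients who need BPT after a non-diagnostic first test, by an amount that depends on biomarker group, and the 12-month QALY window is tied to neither. Second, children's baseline c-ACT and EQ-5D-Y are not carried into the follow-up text or the comparison before and after diagnosis.

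The size depends on the wait between the two tests in biomarker-low patients, which the article does not report. If it were 12 months, the QALY window would hold 12 waiting months under one wording and none under the other. If it were close to the prioritised interval, the difference would be about a month. No QALY or exacerbation bias can be quantified from the document.

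Only secondary outcomes are touched: QALYs and the cost-utility results built on them, asthma control, exacerbations and healthcare use. The primary diagnostic-delay outcome is unaffected. The correction should be made because it is cheap and because the ambiguity follows the comparison of interest.

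**What to change.** 1. Reconcile Setting and Study visits to one start date that every participant has, including those with asthma ruled out and those not yet tested, and say which visit is baseline.
2. Define the QALY window and the exacerbation and healthcare-use windows from that date, with equal length in both biomarker groups.
3. Record the date of the last diagnostic test, and make the comparison before and after diagnosis by actual diagnosis date instead of by questionnaire number.
4. If the first study visit is chosen as the start, state the downside: some low-risk patients will have few or no questionnaires after diagnosis.
5. State that children complete at follow-up the instruments they completed at baseline (c-ACT, EQ-5D-Y), correct the lists in Study visits and Secondary Outcomes, and analyse paediatric and adult utilities separately.

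The cost is protocol wording, the REDCap email triggers and the age-specific questionnaire forms. Neither the testing pathway nor the sample size needs to change.
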